**Figure 1 F1:**
[figure not shown]
**Institutions and participants’ enrollment in the DS1-EI trial by site**. HDJ, *Hopital de Jour* (Day care medical center); IME, *Institut Medico-Educatif* (Special education center).

Each parent provided informed written consent before inclusion. The inclusion criteria were a current diagnosis of ASD confirmed by a clinical assessment based on the International Classification of Diseases, 10th edition criteria and the Autism Diagnostic Interview-Revised (ADI-R) (36); an intellectual handicap with financial compensation from local agencies [*Maison Départementale du Handicap* (MDPH)]; being aged between 5 and 9 years; and having a communication developmental age of 24 months and under based on a Vineland assessment or a 3-year speech delay based on a Psycho-Educational Profile, third edition. We did not exclude children with known organic syndromes and/or non-stabilized neuropaediatric (e.g., seizures) or medical (e.g., diabetes mellitus) comorbidities. However, during the medical assessment, we specifically listed comorbidities. The exclusion criteria were limited to parents’ refusal to participate; family’s plans to change institutions in the short term for any reason; and patient’s severe behavioral impairments that would challenge treatment adherence. Of note, this last exclusion criterion was based on local institution staff decision. Before randomization, each site was requested to assess the IQ of the participants based on the Kaufman Assessment Battery for Children second edition (KABC-II) or, failing that, Vineland scores. Based on these results, dyads of participants matched for sex, age, and developmental quotient (DQ) were formed to limit the risk of bias between groups. Randomization before group allocation to TAU or DS1-EI group was performed by drawing lots in each dyad per site so that each site could have a TAU group and a DS1-EI group of three to four participants each. Randomization was performed by the methodological coordinating team at the Salpêtrière Hospital and was independent from local inclusion sites. TAU was defined as all therapeutic interventions given to a specific child. Given the study duration, we did not recommend not to change children’s therapeutic protocol in the TAU group during the study period. The trial duration was defined as 36 months but included 12-, 18-, and 24-month intermediate assessments.

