### Primary and Secondary Variables

Table 3 summarizes the variables that we planned to measure at enrollment and at several time points throughout the trial. The primary outcome variables were (i) the Childhood Autism Rating scale (CARS), which measures autism severity (38); (ii) the psychoeducational profile, third edition (PEP-3), which measures the total DQ and 5-dimensional DQs related to cognition, receptive language, expressive language, fine motor skills, gross motor skills, and imitation, and (iii) the school’s assessment (39). Secondary variables included the following measures: (i) the *Vineland Adaptive Behavior Scale II* (VABS-II) as a behavioral scale of independence; this scale is assessed through a parent/educator interview and is used to assess the ability of children to perform the daily activities required for personal and social sufficiency. The VABS-II examines four specific domains: Communication, Daily Living Skills, Socialization, and Motor Skills. The subscale scores are totaled to yield an Adaptive Behavior Composite score (40). (ii) The KABC-II standardized neuropsychological assessment to measure intelligence skills. This battery measures Verbal, Performance, Working Memory, Processing Speed and Total quotients (41). (iii) The *Clinical Global Impression* (CGI), which was used to assess global severity (42). (iv) Finally, the *Children Global Assessment Scale* (CGAS) (43). To assess clinical change during the 36-month study, we used a single-blind procedure (independent raters were blind to study group allocation) for all clinical assessments (PEP-3, KABC-II, CARS). Blind assessment was not possible for the measures that required 2-week observations of the participants (CGI, CGAS, school tests) or a parental interview (ADI-R, VABS-II).

**Table 3 T3:** **DS1-EI study procedure and evaluation criteria**.

	Selection	Inclusion	M12	M18	M24	M36
Inclusion criteria	X	–	–	–	–	–
Informed consent	X	–	–	–	–	–
CIM-10 diagnosis	–	X	–	X	–	X
Comorbidity	–	X	–	X	–	X
ADI-R	–	X	–	X	–	X
Vineland	–	X	X	X	X	X
CARS	–	X	–	X	–	X
CGAS	–	X	X	X	–	X
CGI	–	X	X	X	–	X
KABC	–	X	–	X	–	X
PEP-III	–	X	–	X	–	X
School assessment	–	X	X	X	X	X

*ADI-R, Autism Diagnostic Interview-Revised; CARS, Childhood Autism Rating Scale; CGI, Clinical Global Impression; CGAS, Clinical Global Assessment Score; PEP-3, Psychoeducational Profile, 3rd Edition; DQ, developmental quotient; KABC, Kaufmann Assessment Battery for Children*.

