### Statistical Analysis

Statistical analyses will be performed using R Software, Version 2.12.2. To assess whether improvement occurs in both primary and secondary variables, we will use linear mixed models with change in a given variable explained by group exposure (DS1-EI vs. TAU), time (baseline vs. 18 vs. 36 months) and their interaction (group exposure × time). We will also include a random effect and a site effect. This should account for individual heterogeneity, site heterogeneity, variable scores at inclusion, and change specific to DS1-EI within the same statistical regression. For missing data when available, we will use the last observation carried forward. In case of a non-Gaussian distribution, we will study the log transformation (or other transformation when appropriate) to achieve a normal distribution. Lost or drop-out patients will also be compared between groups using a separate non-parametric comparison.

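### The mixed model's three time levels leave no place for the scheduled 12- and 24-month values of four measures; CARS, PEP-3 and KABC are unaffected

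*Protocol article*

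**What the plan says.** The Statistical Analysis section names a single model for all outcomes: "To assess whether improvement occurs in both primary and secondary variables, we will use linear mixed models". The model contains group, time and their interaction, and the levels of time are listed: "time (baseline vs. 18 vs. 36 months)". The rule for missing values follows in the same paragraph: "For missing data when available, we will use the last observation carried forward".

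The visit schedule is wider than these three levels. Participants and Recruitment says that the 36-month trial "included 12-, 18-, and 24-month intermediate assessments". Primary and Secondary Variables introduces Table 3 as the measures planned "at enrollment and at several time points throughout the trial". Two rows of that table are filled at every visit from inclusion to month 36: "School assessment – X X X X X" and "Vineland – X X X X X". The CGI and CGAS rows have inclusion, M12, M18 and M36, with no M24. The CARS, PEP-3 and KABC rows have inclusion, M18 and M36 only.

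The Methods list the school assessment as the third primary outcome. The abstract names only the CARS and the PEP-3 as primary.

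**The concern.** The time factor has been written to fit the CARS, PEP-3 and KABC schedule and then extended to measures with more visits. For those measures the plan does not provide for every value it schedules.

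This matters mainly for children who leave late. A child who leaves between M24 and M36 has an M24 school assessment and Vineland, which is the observation closest to the endpoint. The model has no 24-month level for it. The carry-forward rule does not say whether a value from a visit outside the model may be carried. If it may, a 24-month value stands in for a 36-month one. If it may not, the 18-month value does. The two readings give different 36-month data sets for an outcome that the Methods call primary. The Discussion itself doubts whether enough children will be retained over the 36 months.

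**Working it through.** **Step 1: visits against model levels** (Table 3 against the Statistical Analysis section).

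| Measure | Scheduled visits (months) | Visits without a model level |
|---|---|---|
| School assessment | 0, 12, 18, 24, 36 | 2 of 5 |
| Vineland | 0, 12, 18, 24, 36 | 2 of 5 |
| CGI | 0, 12, 18, 36 | 1 of 4 |
| CGAS | 0, 12, 18, 36 | 1 of 4 |
| CARS | 0, 18, 36 | 0 of 3 |
| PEP-3 | 0, 18, 36 | 0 of 3 |
| KABC | 0, 18, 36 | 0 of 3 |

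**Step 2: what the omitted visits are worth for the 36-month contrast.** The plan gives no precision figure for these measures, so there is none to reproduce.

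Input from the article: 38 and 37 children randomised.

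Assumptions that are not in the article:
- Drop-out is monotone and linear in time, so the share still observed at month t is S(t) = 1 − d·t/36, with d = 0, 0.20 or 0.30. For d = 0.30, the shares last seen at 0, 12, 18, 24 and 36 months are 0.10, 0.05, 0.05, 0.10 and 0.70.
- The correlation R is either compound symmetric (0.5 to 0.85), as a random participant intercept implies, or autoregressive with 0.90 to 0.95 per 6 months.
- Variances are equal, and time is categorical and separate by arm.

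For an arm of size n, the information on the visit means is I = n·Σₖ pₖ·Rₖ⁻¹. Here pₖ is the share with drop-out pattern k, and Rₖ is the correlation matrix of the visits seen in that pattern. The variance of the group difference in change from baseline to month 36 is the sum over both arms of c′I⁻¹c, with c = −1 at baseline, +1 at month 36 and 0 elsewhere.

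The table gives the variance with all scheduled visits divided by the variance with 0/18/36 only, both fitted by likelihood on observed data.

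| Correlation | Five visits, d = 0.20 | Five visits, d = 0.30 | Four visits, d = 0.20 | Four visits, d = 0.30 |
|---|---|---|---|---|
| Autoregressive 0.90 | 0.984 | 0.973 | 0.995 | 0.992 |
| Autoregressive 0.95 | 0.980 | 0.967 | 0.992 | 0.988 |
| Compound symmetric 0.5 | 0.990 | 0.984 | 0.992 | 0.988 |
| Compound symmetric 0.85 | 0.982 | 0.972 | 0.985 | 0.977 |

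With d = 0 every ratio is 1.000, because a saturated time factor gains nothing from intermediate visits when all children are seen at baseline and month 36.

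The five-visit measures (school assessment, Vineland) therefore gain 1.0–3.3% of variance, and the four-visit measures (CGI, CGAS) gain 0.5–2.3%. At the best value, 1/0.967 = 1.034, which is worth 0.034 × 75 ≈ 2.6 children. In standard-error terms, 1 − √0.967 ≈ 1.7%.

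**Step 3: how many children have a late M24 value.** Under the same linear drop-out, 12/36 = one third of leavers go between M24 and M36. With 75 children, 20% drop-out is 15 leavers, of whom 5 go in that window. With 30% it is 22.5 leavers, of whom 7.5 do. For each of them the carried school-assessment or Vineland value is 12 months old at month 36 if M24 is used, and 18 months old if only model visits count.

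**The case against.** The strongest reply has four parts.

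- **Carry-forward may already use M24.** The missing-data sentence does not confine the carried value to the model's visits, and on its plain reading the last observation of a child who leaves after M24 is the M24 value. This stands. A reader might infer that M12 and M24 are thrown away and that month 36 is filled from month 18; the article does not say so. But carrying M24 forward still assigns it to month 36, and the M12 and M24 values of the children who stay have no use in the stated model.
- **The undisputed primary outcomes are not touched.** CARS and PEP-3, the only primary variables in the abstract, are measured at exactly the model's time points, and the Discussion describes blinded assessments at 18 and 36 months. This stands, and it limits the point to four measures that, by the Methods, are not assessed blind. The CGI and CGAS have no M24 value, so the argument about children leaving after M24 does not apply to them.
- **The gain is slight.** This stands. The calculation also compares two likelihood fits; it does not measure the bias from carrying values forward, which depends on trajectories that the article does not give.
- **An article condenses a fuller plan.** This stands only in part. The article does not leave the time factor open: it lists the levels and applies them to all outcomes, against its own Table 3.

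A reader might also take the extra data to be already in hand. The article speaks of planned measurements and reports baseline results only.

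**Conclusion.** The mismatch is real but of low severity. For the school assessment, Vineland, CGI and CGAS, the stated model has no level for some scheduled visits. For CARS, PEP-3 and KABC there is no loss. Whether a primary outcome is affected depends on whether the Methods list or the abstract is followed.

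The precision gain from including the visits is nil with complete data and a few per cent of variance at most with drop-out. That range rests on the assumed 20–30% linear drop-out and the assumed correlations. The larger benefit is in how late leavers are handled: under the same drop-out assumption, about 5 to 8 of 75 children would contribute an M24 value at month 24 and would not have it stand in for month 36. The article does not support a stronger conclusion that collected primary data are discarded.

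**What to change.** For these four measures, define time as a categorical factor with the Table 3 visits: 0/12/18/24/36 months for the school assessment and Vineland, and 0/12/18/36 for the CGI and CGAS. Keep 0/18/36 for CARS, PEP-3 and KABC. Fit by likelihood on the observed values without carrying any forward, and keep the group contrast at 36 months as the target. The likelihood fit assumes that drop-out is at random given the observed values.

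If M12 and M24 are meant for description only, say so. The lists of primary variables in the abstract and the Methods should be reconciled at the same time.

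The cost is a change of wording in the analysis section and a few more mean and covariance parameters. No new data are needed.

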### Number of Participants

From previous studies that showed significant results in terms of efficacy it appears that the minimal number of patients in parallel design was 50 (2). This was the case for behavioral ABA approach [e.g., Ref. (6)] or for developmental ESDM approach [e.g., Ref. (3)]. The number of patients to enroll was based on the following theoretical statistics estimation: for a moderate effect size (α = 0.6), a power fixed at 80%, and a level of significance for a *p*-value fixed at <0.05, 80 patients randomized into two groups are required for a student *t*-test. Given our choice to use linear mixed models (see below) to take into account participant’s effect, we planned to recruit from 70 to 80 participants.

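### Children are randomized within matched dyads, but the stated mixed model has no dyad term; if 36-month change is correlated within dyads, the group × time test is conservative and power is given away.

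*Protocol article*

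**What the plan says.** Participants and Recruitment describes the allocation. After IQ testing (KABC-II or, failing that, Vineland), "dyads of participants matched for sex, age, and developmental quotient (DQ) were formed to limit the risk of bias between groups". Randomization "was performed by drawing lots in each dyad per site", giving three to four children per arm at each site.

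Statistical Analysis explains change in each outcome by group, time (baseline, 18 and 36 months) and "their interaction (group exposure × time"). It continues: "We will also include a random effect and a site effect". The stated aim of these terms is: "This should account for individual heterogeneity, site heterogeneity, variable scores at inclusion".

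The single random effect is not named there, but the reference to individuals points to the participant. Number of Participants agrees, since it justifies mixed models as a way "to take into account participant’s effect". Neither section mentions the dyad, and age and sex are not listed as covariates.

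**The concern.** An analysis should follow the randomization. Here the article carries one layer of the design (site) into the model and omits the layer at which lots were drawn (the dyad). Two children of the same sex, similar age and similar DQ at the same site may well develop alike over 36 months. If they do, the difference between them varies less than the difference between two unrelated children, and a model that treats them as unrelated overstates the standard error of the treatment contrast.

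What is at stake is power. The Discussion says that effect sizes in this field are typically small and doubts that retention will be sufficient. The calculation below also shows that the planned number falls short of its own power target. A needlessly wide confidence interval would raise the chance of missing a real effect.

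**Working it through.** **Inputs from the Protocol article.** Number of Participants: "for a moderate effect size (α = 0.6"), read as a standardized difference; "a power fixed at 80"%; significance level 0.05; 80 children in two groups for a Student t-test. Abstract: 11 institutions; 38 children randomized to DS1-EI and 37 to TAU, so at most 37 complete dyads and at least one child without a partner.

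**Assumed inputs.** Two-sided testing, and the within-dyad correlation rho of the analysed change. The article gives no value for rho, so a range from 0 is shown.

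**Step 1. The article's own figure.** Per arm, n = 2(1.960 + 0.842)²/0.6² = 43.6, rounded up to 44, so 88 in total (90 with the t distribution). One-sided, the totals are 70 and 72. The stated 80 does not reproduce. Two-sided t-test power is 0.755 at 80 children and 0.727 at 75. This is a separate matter, but it shows there is no power to spare.

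**Step 2. Ignoring versus using the dyads, for a change score with SD 1.**

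- Unpaired SE = √(2/37) = 0.232.
- Paired SE = √(2(1 − rho)/37).
- Excess width of the unpaired interval = 1/√(1 − rho) − 1.

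Type I error and power come from 40,000 simulated trials per rho, with 37 dyads and a difference of 0.6.

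| rho | Unpaired SE | Paired SE | Excess width | Type I error, unpaired | Power, unpaired | Power, paired |
|---|---|---|---|---|---|---|
| 0 | 0.232 | 0.232 | 0% | 0.048 | 0.72 | 0.71 |
| 0.1 | 0.232 | 0.221 | 5% | 0.038 | 0.73 | 0.75 |
| 0.2 | 0.232 | 0.208 | 12% | 0.028 | 0.74 | 0.80 |
| 0.3 | 0.232 | 0.195 | 20% | 0.020 | 0.76 | 0.85 |

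The paired test gave 0.048 at every rho, so 0.048 in the first row is the nominal level apart from simulation error.

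**Step 3. The model as stated.** Generalized least squares standard errors were computed for three visits, 37 dyads, 11 fixed site effects and a participant intercept. The assumed variances are 0.6 between and 0.4 within participants.

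- *Correlation in level only.* Moving 0.2 or 0.4 of the between-participant variance to a dyad intercept leaves the 36-month group × time SE at √(4 × 0.4/37) = 0.208, with or without a dyad intercept in the model. Any stable component, whether the child's or the dyad's, cancels when change is taken. Only the baseline group contrast is affected (0.232 falls to 0.208 or 0.180).
- *Correlation in change.* With a dyad-by-time variance v, rho = v/0.4 and the true SE is √(4(0.4 − v)/37). For v = 0.04, 0.08 and 0.12 (rho 0.1, 0.2 and 0.3) this is 0.197, 0.186 and 0.174. The model without the dyad still reports 0.208.

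The loss therefore survives the site effect and the participant effect, but only to the extent that change itself is correlated within dyads.

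**The case against.** Several points on the other side stand.

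- **Purpose.** A reader might infer that the matching was meant to buy precision and that this precision is lost. The article does not support that. It gives limiting bias between groups as the reason for matching, and its sample size uses an unpaired t-test that takes no credit for it. The balance is kept whatever model is fitted.
- **Mechanism.** A reader might also infer that any similarity within dyads inflates the standard error. Step 3 shows that similarity in level does not; only similarity in change does.
- **What the model already captures.** Site is in the model, and Statistical Analysis says that scores at inclusion are accounted for. The matching DQ came from KABC-II or Vineland, which are themselves analysed outcomes, and PEP-3 is expressed as DQs. For these outcomes the baseline score is the DQ matching factor or close to it. The rho that matters is what remains afterwards.
- **Plausible size.** Apart from shared site, matching cannot produce a rho larger than the share of change variance that age, sex and DQ explain. A rho of 0.5 would need half of it, which is unlikely once site and baseline are in the model. Matching may also be loose with three to four children per arm at a site.
- **Ceiling.** Thirty-seven complete dyads is a best case. Table 4 lists 36 TAU children, and losses over 36 months would break further pairs.

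One further objection is that a condensed article leaves the random-effects structure to the analysis plan. That carries less weight here, because the article lists the model terms and says what they are to account for. A fuller document might name the dyad; the stated model does not.

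**Conclusion.** The point holds as a matter of efficiency. The stated model does not reflect the unit of randomization, and two sections of the article tie its only random effect to the participant.

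The consequence is conditional. If change remains positively correlated within dyads after site and baseline, the group × time test is conservative. At rho 0.1 to 0.3 the interval is about 5% to 20% too wide, and using the dyads would add roughly 2 to 9 points of power (0.73 to 0.75, up to 0.76 to 0.85). At rho 0 nothing is lost, and pairing costs about one point.

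These figures assume two-sided 0.05, a standardized difference of 0.6, 37 complete dyads and a rho the article does not give. The power figures come from plain paired and unpaired t-tests, so rho must be read as the correlation left after site and baseline. It would be wrong to infer that the planned result is invalid: the omission does not bias the estimate, and any error in the test is towards caution. The change is worth making because it is nearly free, not because the trial fails without it.

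**What to change.** Name the random effects in full, and add dyad, nested in site, as a random effect that acts on change. This can be a dyad-by-time term in the repeated-measures model, or a dyad effect in a model of change scores adjusted for baseline. A dyad intercept alone is not enough.

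Adjust also for the matching variables age, sex and baseline DQ. In the repeated-measures model, enter them with their interactions with time, since terms that are constant over time cancel from the contrast just as the dyad intercept does.

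Keep children without a partner as single-member dyads. State in advance that if the dyad-by-time variance is estimated at zero or the model does not converge, the analysis falls back on the matching covariates alone. If the dyad is to be left out, say why.

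The cost is small. Dyad membership was fixed when lots were drawn, and the covariates were needed to form the dyads. The model becomes somewhat more complex for at most 37 pairs and three visits. The gains from the dyad term and the covariates overlap and should not be added together. About one point of power is given up if the matching proves uninformative.

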## Discussion

We hope that the current trial will help demonstrate the feasibility of adapting and task-shifting a group of interventions used primarily as early interventions for autism to a school-based context and for use with older individuals with autism and intellectual disabilities. The school-based intervention program [the developmental and sequenced one-to-one educational intervention (DS1-EI)] was adapted from several methods including TEACCH (4, 5), ESDM (3), and ABA (6, 37). The key principles of the method are the intensity, the regular assessments and updating of objectives, the encouragement of spontaneous communication, promotion of skills through play with peers, support of positive behaviors instead of tackling challenging behaviors, regular team supervision, capitalization on teachers’ unique skills, and developmental and sequenced learning (2). The use of sequenced learning (i.e., teacher and activity change every 10–15 min to keep the child’s attention in the context of an anticipated time agenda) is likely the most original proposal. We are aware that treating children with autism and ID is very challenging. The effect sizes are typically small. To balance this risk of failure, we chose to have a rather long study duration with two single-blind assessments at 18 and 36 months. Given the number of sites, which may have introduced bias, we are satisfied that we did not find differences between the groups at baseline.

We are aware that there are several limitations to this trial. First, given the severity of the patients’ conditions, the study duration and the nature of the intervention, only a single-blind for the primary variables was feasible. Second, the method used to randomize participants (to limit the bias of TAU) combined with the study duration and the supervision of local teams is likely to modify local staff practice and to lead to some DS1-EI principles being used in the TAU group as well. Third, because our public sponsors required us to balance hospital/academic/large city sites and non-hospital/remote rural area sites, we cannot assume that we will achieve a uniform level of adherence to the program from one site to another. Finally, given the study duration, we do not know whether we will retain a sufficient number of patients in the program to maintain the statistical power needed for per protocol analyses.

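### Carrying the last observation forward can bias the 36-month group contrast in an unknown direction, and the planned mixed model does not need it

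*Protocol article*

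**What the plan says.** The Statistical Analysis section of the protocol article describes one model for primary and secondary variables. It is a linear mixed model with group, "time (baseline vs. 18 vs. 36 months) and their interaction (group exposure × time"), and it continues: "We will also include a random effect and a site effect". For incomplete data it gives one rule: "For missing data when available, we will use the last observation carried forward". The rule is not confined to a sensitivity analysis and no other method is named. The only further provision is a non-parametric comparison of lost children between groups, which describes dropout but corrects nothing.

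The Participants and Recruitment section (text after Figure 1) says: "The trial duration was defined as 36 months but included 12-, 18-, and 24-month intermediate assessments". Table 3 shows that those intermediate visits differ by instrument. CARS and PEP-3 are measured only at inclusion, M18 and M36. The school assessment is measured at inclusion, M12, M18, M24 and M36. The Primary and Secondary Variables section lists all three as primary. On retention, the Discussion says only that the authors do not know whether enough children will stay "to maintain the statistical power needed for per protocol analyses".

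**The concern.** A carried value asserts that the score at month 36 equals the last score seen. For CARS and PEP-3 that score is 18 months old if the child left after M18, and 36 months old if the child left before M18. In the second case the child contributes exactly zero change at both follow-up visits. For the school assessment the gap can be shorter, because M12 and M24 also exist, but the assumption is the same.

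The inclusion criterion is "being aged between 5 and 9 years", and follow-up lasts three years, so stable scores cannot be presumed. If scores move, freezing them pulls each arm's mean change towards zero in proportion to that arm's losses. The between-arm difference then depends partly on who left and when. The model also treats the filled values as measurements, so their uncertainty is understated.

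A linear mixed model can be fitted to incomplete records directly and is valid if data are missing at random given what was observed. Carrying values forward replaces that assumption with a stronger and less plausible one.

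**Working it through.** **Inputs from the article.** Visits for CARS and PEP-3: 0, 18 and 36 months (Table 3). Arms: 38 and 37 randomized (abstract). Baseline CARS SD: 7 in DS1-EI (Table 4), used only to convert units. A difference of 0.6 SD is borrowed from the Number of Participants section ("for a moderate effect size (α = 0.6), a power fixed at 80") as a reference size. The article gives no figure for missing data, so there is none to reproduce. The stated total of 80 children does not enter this check.

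**Assumptions, none of them in the article.** Dropout of 10% to 30% per arm by month 36, half before M18 and half after. Change is linear in time. Children who leave would have followed their arm's mean path.

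**Formula.** Let *C* be an arm's true mean change at month 36 and *p* its dropout. A share 1 − *p* contributes *C*, a share *p*/2 contributes *C*/2 (carried from M18), and a share *p*/2 contributes 0 (carried from baseline). The expected change after carrying forward is

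*C* × (1 − *p* + *p*/4) = *C* × (1 − 0.75*p*).

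The multipliers are 0.925 for 10% dropout, 0.85 for 20% and 0.775 for 30%.

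**True contrast 0.6 SD (DS1-EI changes 1.2, TAU 0.6).**
- 20% in both arms: 1.2 × 0.85 − 0.6 × 0.85 = 1.02 − 0.51 = 0.51.
- 30% in both arms: 1.2 × 0.775 − 0.6 × 0.775 = 0.93 − 0.465 = 0.465.
- 30% DS1-EI, 10% TAU: 1.2 × 0.775 − 0.6 × 0.925 = 0.93 − 0.555 = 0.375.
- 10% DS1-EI, 30% TAU: 1.2 × 0.925 − 0.6 × 0.775 = 1.11 − 0.465 = 0.645.

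**True contrast 0 (both arms change 0.6).**
- 20% in both arms: 0.51 − 0.51 = 0.
- 10% DS1-EI, 30% TAU: 0.555 − 0.465 = 0.09; reversing the arms gives −0.09. In CARS points this is 0.09 × 7 ≈ 0.6.

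**Simulation.** 4000 trials per setting, 38 vs 37 children, correlation 0.7 between visits. Dropout was either completely at random or dependent on the last observed score. Carried-forward month-36 values were compared between arms with baseline adjustment, and a likelihood analysis was run on the incomplete data.

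| Setting (dropout DS1-EI/TAU) | True | Carried forward | Rejection rate, carried forward | Likelihood, no imputation |
|---|---|---|---|---|
| No effect, 20%/20% | 0 | 0.005 and −0.002 | 5.9% and 5.4% | 0.004 and −0.001 |
| No effect, 10%/30% | 0 | 0.086 and 0.130 | 7.9% and 12.4% | 0.002 and 0.003 |
| Effect, 20%/20% | 0.6 | 0.515 and 0.500 | 82.6% and 75.9% | 0.604 and 0.595 |
| Effect, 30%/10% | 0.6 | 0.385 and 0.335 | 57.8% and 43.6% | 0.597 and 0.600 |

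Each pair gives random dropout first, then score-dependent dropout. The random-dropout column agrees with the closed form. With equal dropout and equal change the false-positive rate stayed close to 5%, so I put no size on the understated uncertainty. That simplified month-36 comparison is not the full mixed model.

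**The case against.** The case on the other side has four parts.

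First, nothing in the article fixes the size. Equal dropout with equal change gives no bias, and equal dropout with a real effect only shrinks it. The false-positive rates above need a 20-point gap in dropout that nobody has reported. This stands, and it is why the point is that the method can bias the contrast. A reader might infer that the 36-month result is certainly biased; the documents do not show that.

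Second, loss may be modest. Families planning to change institution in the short term are excluded, and dropouts will be compared between arms. A reader might infer that the authors expect heavy losses, but the Discussion states only that retention is uncertain. Nor does Table 4's TAU column of 36, against 37 randomized, show loss to follow-up. It is an unexplained gap in a baseline table, and a child without a baseline value has nothing to carry forward.

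Third, PEP-3 is reported as a developmental quotient, so carrying it forward holds the quotient constant, not the skill level. If the quotient is developmental age over chronological age (the article does not define it), cognition at 22.3 and age 6.92 years is 0.223 × 6.92 × 12 = 18.5 months. Three years later the same quotient implies 0.223 × 9.92 × 12 = 26.5 months. With no progress it would be 18.5 / (9.92 × 12) = 15.6%, that is 6.7 points lower, or 6.7 / 11.1 = 0.6 SD. It is tempting to read that 0.6 SD as bias in the treatment effect. It is the error for one child who leaves before M18 and then makes no progress; a child developing at a constant quotient would have no error. A constant quotient is nevertheless untested.

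Fourth, the mixed model also rests on an assumption, missing at random, and its estimates vary more. In the 20%/20% effect setting the standard deviations were 0.185 against 0.176. The estimate relative to its standard deviation is still better without imputation: 0.604 / 0.185 = 3.3 against 0.515 / 0.176 = 2.9.

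An unseen analysis plan does not remove the point, because the article itself states this method.

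**Conclusion.** The concern holds in a conditional form. Carrying the last observation forward is the only stated rule for missing data. It applies to the primary variables (CARS, PEP-3 and the school assessment), and it precedes a model that can use incomplete records as they are. It can bias the 36-month contrast. With equal dropout it shrinks a real effect, with unequal dropout it can move the contrast either way, and it is unbiased only in special cases. It therefore cannot be defended as conservative.

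Over 10% to 30% dropout, with half the loss before M18 and linear change, the closed-form bias ran from −0.225 SD (0.375 against 0.6) to +0.09 SD (0.09 against 0). These sizes are illustrative. The Discussion notes that effects in this population are typically small, so shifts of this order would matter if they occurred. What is certain is that the method is a poor choice; how large the bias will be is not known.

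**What to change.** In the Statistical Analysis section, delete last observation carried forward as the primary method. State that the planned mixed model will be fitted by REML to all observed values of all 75 randomized children, in the arm to which they were randomized. State that the 36-month group difference will be estimated from that model, with missing at random as the working assumption. Last observation carried forward may stay as a sensitivity analysis at most.

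A sensitivity analysis that departs from missing at random would be sensible, given three years of follow-up, but it is optional and its form can be left to the analysis plan. The planned comparison of dropouts between groups can stay as a description.

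The cost is a few sentences of protocol or analysis-plan wording. No new data, visits or children are needed.
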